## Abstract

**Background:**

Virtual healthcare solutions are proposed as a way to combat the inequity of access to healthcare in rural and remote areas, and to better support the front-line providers who work in these areas. Rural provider-to-provider telehealth (RPPT) connects rural and remote clinicians to a ‘hub’ of healthcare specialists who can increase access to emergency and specialised healthcare via an integrated model. Reported benefits for the place-based provider include enhanced knowledge, expanded professional development opportunities, improved scope of practice, and increased confidence in treating more complex cases. These reported benefits could have implications for supporting and futureproofing our health workforce in terms of productivity, burnout, recruitment, and retention.

**Methods:**

The research uses an explanatory sequential mixed methods approach across multiple phases to evaluate the current implementation of Western Australia Country Health Service's (WACHS) Command Centre (CC) services and explore factors associated with their differential use. The primary population of interest and participants in this study are the place-based providers in country Western Australia (WA). Patient data constitutes the secondary population, informing the access and reach of CC services into country WA. Data collection will include service data, an online survey, and semi-structured interviews with the primary population. The data will be interpreted to inform evidence-based strategies and recommendations to improve the implementation and sustainment of RPPT.

**Discussion:**

Innovative and sustained workforce models and solutions are needed globally. Virtual healthcare, including provider-to-provider models, demonstrate potential, especially in rural and remote areas, designed to increase access to specialised expertise for patients and to support the local workforce. This research will generate new data around behaviour, perceptions, and value from the WACHS rural and remote workforce about provider-to-provider telehealth, to explore the implementation and investigate strategies for the long-term sustainment of RPPT services.

## Background

People living in rural and remote areas consistently experience poorer health outcomes compared to people living in urban or metropolitan areas.^
1
^ Remoteness is linked to poorer health outcomes and a higher burden of disease largely driven by reduced access to healthcare.^1,2^ Access to health services in rural and remote areas is not only a challenge of physical distance, but the demand for services regularly outstrip supply.^
3
^ This is partly due to a workforce shortage, a problem experienced globally.^
2
^ Workforce shortages and high staff turnover also impact the effectiveness of services, with research showing an association between workforce issues and a reduction in patient health outcomes, significantly higher hospitalisation rates, and decreased continuity of care.^4,5^ The workforce shortages in Australia are projected to progressively intensify over the next 40 years, partly due to an ageing population reducing the available labour force.^
6
^ Modelling based on Commonwealth of Australia data has estimated that the workforce needs to be four times more productive in terms of patient throughput and efficiency to meet future demand.^
7
^

### Virtual health solutions

Proposed as a way forward, virtual health solutions aim to build, strengthen, and futureproof our healthcare system.^8,9^ Virtual health solutions, encompassing the terms telehealth and telemedicine, have been relied on for decades in rural and remote areas as a way to increase access to healthcare due to the geographical distances and poor economies of scale.^
10
^ Recently, there has been a global acceleration and innovation in virtual healthcare, largely due to COVID-19 pandemic, including a rapid rollout of services that can complement face-to-face options.^
11
^ This has been seen as beneficial for both consumers and the health system but has emerged spontaneously and opportunistically rather than rigorously and systematically.^12,13^ For consumers, research suggests one size does not fit all. While there are many aspects of virtual healthcare that are valued, such as having choice and flexibility, consumers generally do not want virtual health to replace face-to-face services.^14,15^ In terms of the health system, there are benefits in productivity through the optimisation of staff time, including less need for travel, enabling a clinician to convert travel time to clinical time, especially in rural and remote areas.^
16
^ Less travel also translates to lower costs to both the provider and patient. The main benefit of virtual healthcare is providing access to services where they were previously not available. However, an increase in access has the potential for excess use and therefore not necessarily a reduction in costs.^
16
^

On the contrary, there is commentary about the unintended consequences of virtual health. This includes the risk of an increase in the digital divide for older and vulnerable populations, a further fragmentation of services, and concerns virtual health will replace face-to-face services, increasing local workforce shortages.^11,17,18^ Given these considerations, research on the effectiveness, value, and acceptance of virtual services is necessary to build an evidence base of virtual healthcare options so that a more systematic and strategic approach to integrated healthcare can be implemented.

### Rural provider-to-provider telehealth

Rural provider-to-provider telehealth (RPPT) services commonly involve connecting rural front-line providers (clinicians) to a ‘hub’ of urban specialists. Previous authors have defined RPPT as ‘any form of interactive support using telecommunications technology provided to health care professionals while they are caring for rural patients and populations’.^
19
^ The aim of RPPT is to increase access to healthcare that would otherwise be unavailable. RPPT services are comprised of virtual patient assessments, clinical consultations, mentoring, supervision, and continuing education between healthcare professionals in the inpatient, outpatient, and emergency settings.^19,20^ Totten et al.^
19
^ conducted a systematic review of RPPT services looking at the uptake of services, the effectiveness of the services, the barriers and facilitators to implementation and sustainability, and recommendations for strengthening future research. The review found a growing use globally for RPPT, and patient health outcomes which were similar or better when compared to no virtual health support.^19,21^ Barriers and facilitators were identified to the implementation of RPPT, including well-functioning technology, sufficient resources, and adequate payment as facilitators, and a lack of understanding of the rural context as a barrier.^19,21^ Methodological weaknesses were found in the studies examined, including less rigorous designs susceptible to bias, small sample sizes, an absence of program theory and analytical frameworks, and a lack of clearly described research questions.^19,21^

The Totten et al.^
19
^ systematic review reports benefits for front-line clinicians receiving virtual education and mentoring.^
22
^ These included improved knowledge, skills, and confidence, increased professional development opportunities, increased scope of practice, and improved safety and quality outcomes.^
19
^ It is not known if these benefits translate to decreased burnout, workforce turnover or improved retention. It is suggested that RPPT can decrease the total cost of care, but it is not known to what extent. A scoping review by Snoswell et al.^
16
^ recommends that any implementation of virtual health services should be motivated by aspects other than cost reduction. The Totten et al.^
19
^ review, and following workshop convened by the National Institutes of Health in the United States,^
20
^ identified key knowledge gaps and specific recommendations to build evidence on the emerging use and effects of RPPT. Highlighted was the inconsistent evaluation, implementation, and sustainment of these services, recommending that conceptual frameworks be used, and contextual factors be considered. Additionally, Wakefield et al.^
20
^ calls for new research efforts to understand the value and effects these services deliver, with an aim to improve health outcomes for rural and remote patients, by supporting the local workforce and improving access to healthcare.

This research intends to strengthen the evidence base of RPPT by providing methodologically sound research to fill knowledge gaps and recommendations identified by Totten et al.^
19
^ and Wakefield et al.^
20
^ Recommendations identified by these authors^
20
^ that this research intends to cover include:
The variation of uptake across diverse settings, organisational structures, and provider types.The standardisation of measures across multiple sites to assess outcomes and impact.Evaluate whether RPPT impacts rural provider recruitment and retention.Engage providers to shape and evaluate RPPT to better meet community and population needs.Examine sociocultural factors that may influence uptake, outcomes, and sustainability.Use statistical approaches to minimise selection bias and address confounding effects.Employ mixed methodologies to triangulate qualitative and quantitative results.Specifically, this research will utilise the Western Australia Country Health Service (WACHS) Command Centre (CC) as an example of RPPT , to assess the differential implementation of RPPT across over 100 sites in country Western Australia (WA). The CC operates 24 h a day, 7 days a week, specialising in emergency, acute, and specialty clinical services, and staffed by clinical and non-clinical staff who support over 6000 front-line providers in country WA.^
23
^ The purpose of the CC is to virtually support the delivery of, and equitable access to, high-quality healthcare for people in country WA, and to complement place-based service provision.

Therefore, the overall aim of this research is to increase the understanding of provider-to-provider telehealth in rural and remote settings, including its value, benefit, and sustainment, in the WACHS.

### Objectives

Evaluate the implementation of RPPT in country WA.Explore factors associated with the differential use of RPPT in country WA.Triangulate and synthesise results to develop evidence-based recommendations to improve the implementation and sustainment of RPPT.

## Methods

### Setting

WACHS delivers healthcare services to over 550,000 people across 2.5 million square kilometres.^24,25^ There are 103 WACHS-run health facilities, including six large regional hospitals, 15 medium-sized district hospitals, 48 small hospitals, and 34 health centres and nursing posts across seven geographically dispersed regions. There are additional non-WACHS health facilities and Aboriginal Medical Services that are outside the scope of this research.

The majority of smaller health facilities are operated by generalist nurses, with medical cover provided by a local general practitioner. Each region is unique in its population, geography, health needs, and service availability, and all classified as rural and remote according to the Australian Statistical Geography Standard (ASGS) Remoteness Structure.^
1
^ The ASGS is based on the road distances people have to travel for services.^
1
^
Figure 1 shows the seven WACHS regions, overlayed with the measure of remoteness.

**Figure 1. fig1-20552076241242790:**
[figure not shown]
WA country health service geographical service delivery area, by region and remoteness. 
WA: Western Australia.

### Model of service

The WACHS CC began operations in 2012 as the Emergency Telehealth Service (ETS), a virtual health solution to support diagnosing, treating, and managing patients in local regions.^
26
^ The ‘Command Centre’ was officially launched in 2019 from recommendations of the Department of Health, Western Australia's Sustainable Health Review.^
27
^ A suite of services have since been implemented, beginning with the Inpatient Telehealth Service, and Mental Health Emergency Telehealth Service, and more recently, the Midwifery and Obstetrics Emergency Telehealth Service,^
28
^ and the Palliative Care Afterhours Telehealth Service.^29,30^ While these services differ in their functionality and purpose, they all deliver provider-to-provider specialist and clinical advice via virtual means, supporting the front-line clinicians caring for patients in rural and remote areas. The CC's Clinical services aims are as follows:
Facilitate appropriate decision making in the treatment and care of country patients.Support our place-based workforce by providing guidance, advice, and access to specialist knowledge to help provide the best care possible for rural and remote patients.Build a collaborative, integrated workforce, blending place-, and remote-based clinicians to deliver care to the highest possible quality and safety standard and in the most culturally appropriate way.Unlike other virtual or telehealth care, which is often between the patient and provider, these services are usually between the rural and remote front-line provider, with the patient present, and the specialist provider. The suite of CC services is enabled in 87 of the 103 health facilities.

### Population

While the objective of the CC is to improve healthcare for the rural and remote population, the primary population for this research is the direct receivers of the CC services, the approximately 6000 place-based health professionals in country WA. This includes nurses, midwives, medical officers, and medical practitioners who work across WACHS health facilities. Allied health professionals are not in scope for this research. The secondary population is the patients attending these rural and remote health facilities, often in emergency or acute situations. Patient ‘service contacts’ represent the volume and characteristics of activity at each health facility and are crucial to assessing implementation status. There has been approximately 200,000 service contacts across the suite of services since 2012.

### Design

The research will use an explanatory sequential mixed methods approach^
31
^ across multiple phases, displayed in Figure 2. This type of design is suitable for a real-life complex healthcare service, allowing greater understanding from multi-faceted sources.^
32
^ The CC is an active and dynamic set of healthcare services that have been implemented for varying lengths of time, and are operating within a larger public health system. The study will begin with quantitative data collection and analyses, followed by a qualitative phase used to explain and better understand the quantitative results.^
31
^ This will be followed by an interpretative phase where data are triangulated and synthesised to develop evidence-based recommendations for implementation improvements.

**Figure 2. fig2-20552076241242790:**
[figure not shown]
Research design.

An Advisory Research Group will be formed at the formative stage of this research, with participants from key areas of WACHS, including representation from (a) the CC, (b) Research, Innovation and Development, (c) Strategy and Change, (d) Data Analytics, (e) provider/s from rural and remote areas, (f) health service consumers, and (g) the Research Team. This group will meet up to four times per year with a role to provide advice, feedback, and appropriateness of research components.

### Proposed phases, data collection, and analyses

There are three phases for this research: CC service data analyses; a survey and semi-structured interviews; and an interpretation and testing of results phase. These are intended to answer the research questions outlined in Table 1, mapped to research objectives. Data to be collected and analysed are described in Table 2, mapped to the expanded reach, effectiveness, adoption, implementation, maintenance (RE-AIM), and implementation outcomes framework (IOF) framework definitions defined by Reilly et al.^
33
^

**Table 1. table1-20552076241242790:** Research questions mapped to objectives.

Objective	Research questions
1. Evaluate the implementation of rural provider-to-provider telehealth services in country WA.	What is the reach and adoption of Command Centre services over time? What are the differences in reach and adoption across regions, sites, and health facility types? What are the differences in characteristics of patients involved in an episode of care from Command Centre services? What proportion of WACHS hospital presentations are referred to the Command Centre?
2. Explore factors associated with the differential use of rural provider-to-provider telehealth.	What are the differing behaviours, attitudes, and perceptions front-line providers have for Command Centre services? Is there a difference in the characteristics/demographics of providers who use Command Centre services? What do providers see as the benefit and value of the Command Centre services? What are the perceived risks to the place-based provider in using Command Centre services? What are the main reasons providers do not use Command Centre services? Did environmental or policy changes (system/outer context factors) influence service reach and adoption?
3. Triangulate and synthesise results to develop evidence-based recommendations to improve the implementation and sustainment of rural provider-to-provider telehealth.	What are the core components of Command Centre services? What adaptations have been made to Command Centre services to better suit local contexts? What factors potentially influence the sustainment of the Command Centre? How can the Command Centre services be improved to better integrate virtual healthcare and support the place-based workforce?

WACHS: Western Australia Country Health Service; WA: Western Australia.

**Table 2. table2-20552076241242790:** Data measures guided by the expanded RE-AIM and IOF.^
33
^

RE-AIM dimension	Expanded RE-AIM & IOF definition	Data measure	Data collection
Reach	Number of individuals exposed to the intervention	Number of CC patient contacts (by site, health facility type, region) for each command centre service	Service data
	Proportion of intended audience who participate in the intervention	Proportion of CC patient contacts compared to total health facility presentations	Service data
	Representativeness of individuals relative to the intended population	CC Patient contact characteristics (age group, sex, postcode, Aboriginal and/or Torres Strait Islander status, priority category, diagnosis)	Service data
Effectiveness	The degree to which the intervention is producing its intended effects while assessing potential unintended consequences and changes in quality of life	Degree to which staff agree that the intended objectives of the CC are being met	Survey Interviews
Adoption	Number of settings that participate in or are exposed to the intervention. (Organisational level)	Number of sites where CC services and infrastructure have been implemented (by health facility type and region) for each CC service	Service data
	Proportion of the intended settings who deliver or are exposed to the public health intervention. (Organisational level)	Number of sites actively using CC services compared to where services and infrastructure have been implemented by not being actively used. Determined by patient volume.	Service data
	Representativeness of settings relative to the intended population who participate in or are exposed to the public health intervention. (Provider level)	Number and characteristics of front-line providers using the CC (by site, health facility type, region) for each service	Survey
	Antecedent assessment of service recipient perception (Provider level)	Front-line provider attitudes and perceptions of CC services Normalisation MeAsure Development (NoMAD) questionnaire^ 39 ^	Interviews Survey
Implementation	Consistency of delivery as intended and in the time required across staff and organisations	Fidelity: Rollout of services according to implementation plan	Service data Interviews Project initiation documents Operational guidelines
	Adaptation Assessing indicators of adaptation prior to, during, and following implementation of the intervention	Local adaptations Cultural adaptations	Survey Interviews Project initiation documents Operational guidelines
Maintenance (individual level)	The extent to which the intervention's primary outcome is sustained ≥6 months	Provider REport of Sustainment Scale^ 40 ^	Service data Survey
Maintenance (organisational level)	The public health intervention becomes institutionalised or part of the routine organisational practices and policies	Reach and adoption over time Normalisation MeAsure Development (NoMAD) questionnaire^ 39 ^	Service data Survey

RE-AIM: reach, effectiveness, adoption, implementation, maintenance; IOF: implementation outcomes framework.

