#### Phase 1: command centre service data analyses

Data from each of the CC services will be collated from the date of implementation, or when useful data collection commenced, to the date of data extraction. These vary based on the service, with dates to be outlined on analyses.

Variables to be collected and analysed for each service are framed around the evaluation of implementation status and implementation outcomes, integral and proceeding to successful service and clinical outcomes.^
35
^ Service data will be collected for all ‘service contacts’ across the 103 WACHS-run health facilities, which were referred to the CC. No individual staff data are collected in the service data, therefore ‘Episode’ volume will be used to demonstrate the reach (patient level) and adoption (organisational level), as outlined in Table 2.

CC service data will be analysed via descriptive statistics including measures of frequency, percentages, central tendency, and variation. The analyses will describe each CC service, by site, by region, and by health facility type. Prior to analyses, the data will be transformed into a suitable format across the services to enable cross-tabulation across variables. The data will also be checked for missing or not applicable data or the presence of any anomalies. Inferential statistics will be used to test for analysis of variance between patient contacts (dependent variable) and the region, health establishment type, and site (Independent variables), per service.^
41
^

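### Representativeness of reach is to be measured on Command Centre contacts alone, so the stated data cannot show reach by patient group

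*Protocol article*

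**What the plan says.** Three rows of Table 2 cover Reach. The first counts CC patient contacts. The second is "Proportion of CC patient contacts compared to total health facility presentations", and Table 1 has a matching question on the share of hospital presentations referred. The third is defined as "Representativeness of individuals relative to the intended population"; its measure is "CC Patient contact characteristics (age group, sex, postcode, Aboriginal and/or Torres Strait Islander status, priority category, diagnosis"), with service data as the source.

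The Phase 1 section describes the extract: "Service data will be collected for all ‘service contacts’ across the 103 WACHS-run health facilities, which were referred to the CC". On analysis it says: "The analyses will describe each CC service, by site, by region, and by health facility type". It adds an analysis of variance of patient contacts on region, establishment type and site. No patient characteristic is among the independent variables, and no comparison of referred with non-referred patients is described.

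The Population section is wider than the extract: "The secondary population is the patients attending these rural and remote health facilities, often in emergency or acute situations". The Table 1 question on patient characteristics is narrower: "What are the differences in characteristics of patients involved in an episode of care from Command Centre services". It concerns patients who had a CC episode.

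**The concern.** Representativeness is a comparison: the profile of those reached is set against the profile of those who could have been reached. The third Reach row states the comparison in its definition and then gives a measure that holds only one side of it.

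A profile of contacts cannot separate two explanations for a low share of some group: the group may seldom attend these facilities, or it may attend and be referred less often. The remedies differ, and Phase 3 is meant to turn the results into recommendations. Patient data are there to inform the access and reach of the services, and the Theoretical frameworks section lists equity among the indicators of success. A contact profile reported under the label of representativeness could therefore be read as evidence of fair or unfair reach when it shows neither.

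**Working it through.** The plan states no figure on this point, so there is nothing to reproduce. The check is whether the stated measures are enough to determine reach by patient group.

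**Quantities**
- r: overall proportion of presentations referred. Available from the second Reach row.
- s: a group's share of CC contacts. Available from the third Reach row.
- q: the same group's share of all presentations. Not stated as obtained anywhere in the article.

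**Formulas.** With N presentations there are rN contacts, of which srN come from the group, and qN presentations come from the group. Hence:
- reach in the group = s × r / q
- reach in the rest = (1 − s) × r / (1 − q)
- ratio of the two = (s / q) / ((1 − s) / (1 − q))

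The overall proportion r cancels from the ratio. Knowing it well adds nothing to the comparison between groups; q is needed.

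**Illustration.** All values are assumed and none comes from the documents: s = 30%, r = 10%.

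| q | Reach in group | Reach in rest | Ratio |
|---|---|---|---|
| 15% | 0.30 × 0.10 / 0.15 = 20.0% | 0.70 × 0.10 / 0.85 = 8.2% | 2.43 |
| 20% | 0.30 × 0.10 / 0.20 = 15.0% | 0.70 × 0.10 / 0.80 = 8.75% | 1.71 |
| 30% | 0.30 × 0.10 / 0.30 = 10.0% | 0.70 × 0.10 / 0.70 = 10.0% | 1.00 |
| 45% | 0.30 × 0.10 / 0.45 = 6.7% | 0.70 × 0.10 / 0.55 = 12.7% | 0.52 |

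The stated outputs, s and r, are the same in all four lines, yet the lines describe over-reach, equal reach and about half the reach of other patients.

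**Does splitting by place help?** Dividing the second row by site or region gives a separate r for each place. That can show where reach is low. Within any one place the same formula applies, and q for that place is still missing.

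**Source of the denominator.** Table 2 gives service data as the source of total presentations, but the Phase 1 section describes service data as referred contacts. Either the label in Table 2 covers more than the Phase 1 extract, or the source of the denominator has not been stated. The text does not settle which.

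**The case against.** The strongest reply is that a table cell in a condensed article is shorthand. The definition beside it already names the reference, the Population section supplies a candidate for it, and the file that provides the reference distribution is the kind of detail a full protocol holds. This has some force, but the article is not silent here: it gives a definition, a measure with six fields and a source, and the measure as written does not meet the definition. Nothing in the planned analyses supplies the missing side.

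Several stronger readings are tempting and are not supported:
- *That no characteristics will be collected for non-referred patients, or that presentations enter only as a bare count.* The article says neither. It does not state the form in which total presentations will be obtained, and the ambiguity over their source leaves room for more.
- *That the study has no comparator for reach.* It has one for overall reach. The gap is confined to reach by patient characteristic.
- *That the study fails its own equity aim.* Equitable access is the stated purpose of the CC. The study's aim is to understand provider-to-provider telehealth, patients are its secondary population, and a contact profile can answer the Table 1 question on patients with a CC episode.
- *That some group is in fact under-referred.* The documents give no data on this, and the shares above are invented for illustration.

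It is also fair to say that the availability of all six fields for every presentation is undocumented.

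**Conclusion.** The concern holds for the third Reach row. As written, that row yields a profile of CC contacts, and adding the overall proportion referred does not turn it into a statement about representativeness. Under-reach of a patient group and the case mix of attenders would give the same output.

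No size for this study can be derived from the documents. In the assumed example the ratio runs from 2.43 to 0.52 as the unknown presentation share goes from 15% to 45%. The conclusion does not depend on those values, because q is absent from the stated measures and the ratio cannot be formed without it. It does rest on taking the article's text as the plan: if a breakdown of presentations by characteristic is already intended, the fault is in the Table 2 wording and is cured by stating it. The change is worth making because the overall proportion already requires data on total presentations.

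**What to change.** Obtain the total presentations already needed for the second Reach row, for the same CC-enabled facilities (87 of the 103, according to the Model of service section) and the same dates as the contacts. Have them tabulated by those of the listed characteristics that are recorded for all presentations, such as age group, sex, Aboriginal and/or Torres Strait Islander status, postcode and priority category. Aggregated counts are enough. Report the proportion referred within each stratum, by site or region. Change the Table 2 measure to: CC contacts compared with all presentations at enabled facilities, by characteristic. State the source of the presentations data. Modelled rate ratios with site effects are optional.

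The cost is a wider data request and possibly an ethics or data-access variation, with field availability to be checked first. If the breakdown cannot be obtained, relabel the row as a description of CC contacts and draw no conclusion on representativeness from it.

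### Table 2 defines site adoption as a proportion of intended settings but measures it as active against inactive sites, judged by patient volume, which can confound adoption with facility size

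*Protocol article*

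**What the plan says.** In Table 2 (Proposed phases, data collection, and analyses), the second Adoption row gives the definition as "Proportion of the intended settings who deliver or are exposed to the public health intervention". The data measure beside it is a count of active sites "compared to where services and infrastructure have been implemented by not being actively used. Determined by patient volume". The words 'by not' read as a slip for 'but not'.

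The text under Phase 1: command centre service data analyses repeats the choice. Because the service data identify no individual staff, episode "volume will be used to demonstrate the reach (patient level) and adoption (organisational level), as outlined in Table 2".

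Three other places bear on the point:

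- **Setting** lists 103 facilities: six large regional hospitals, 15 medium-sized district hospitals, "48 small hospitals, and 34 health centres and nursing posts".
- **Model of service** states: "The suite of CC services is enabled in 87 of the 103 health facilities".
- **Table 1** asks how reach and adoption differ by region, site and health facility type.

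The Reach block of Table 2 already plans a size-adjusted quantity, contacts relative to all presentations at the facility. It is not linked to adoption.

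**The concern.** There are two faults in one row.

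**The denominator.** A proportion of intended settings needs the intended settings underneath. The stated comparator is the enabled sites that are not active, so the active sites are missing from it. The article also does not say whether the intended settings are the 87 enabled facilities or all 103.

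**The criterion.** Patient volume depends on how many patients a facility sees and how long the service has been available there, as well as on how readily staff use it. The Discussion acknowledges that services started at various times and locations, and Phase 1 data run from each service's start (or from when useful data collection began) to extraction. Smaller facilities make up most of the network. If activity is judged on volume alone, a difference in adoption between facility types may partly or wholly reflect facility size.

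This matters because adoption by facility type is a named research question, adoption over time is reused under Maintenance, and Phase 3 uses the integrated results to choose strategies for improving adoption.

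**Working it through.** The article states no adoption figure, cut-off or expected number of active sites, so there is no figure of the plan's own to reproduce. The checks below show how the two faults behave.

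**1. Facility mix (from Setting and Model of service)**
- 6 + 15 + 48 + 34 = 103, which agrees with the stated total.
- Small hospitals, health centres and nursing posts: 48 + 34 = 82; 82/103 = 80%.
- Enabled: 87/103 = 84.5%; not enabled: 103 − 87 = 16.

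**2. Denominator**

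Let A be the number of active sites (assumed; the article gives none). The literal comparison is A/(87 − A). The two candidate proportions are A/87 and A/103.

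| A (assumed) | A/(87 − A) | A/87 | A/103 |
|---|---|---|---|
| 20 | 20/67 = 0.30 | 23.0% | 19.4% |
| 44 | 44/43 = 1.02 | 50.6% | 42.7% |
| 70 | 70/17 = 4.12 | 80.5% | 68.0% |
| 80 | 80/7 = 11.4 | 92.0% | 77.7% |
| 87 | undefined | 100% | 84.5% |

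The literal comparison has no upper bound and fails when every enabled site is active. With A = 70, choosing 87 or 103 as the denominator moves the result by 80.5 − 68.0 = 12.5 percentage points.

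**3. Volume criterion**

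Assumptions: yearly contacts at a site are Poisson with mean m = uptake × presentations. Uptake, presentations and cut-offs are illustrative. The entries are P(contacts < cut-off), the chance that a site is labelled inactive.

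| Uptake | Presentations/year | m | Cut-off 1 | Cut-off 12 | Cut-off 52 |
|---|---|---|---|---|---|
| 2% | 200 | 4 | 1.8% | 99.9% | ~100% |
| 2% | 2,000 | 40 | ~0 | ~0 | 96.1% |
| 2% | 30,000 | 600 | ~0 | ~0 | ~0 |
| 5% | 200 | 10 | ~0 | 69.7% | ~100% |
| 5% | 500 | 25 | ~0 | 0.1% | ~100% |
| 5% | 30,000 | 1,500 | ~0 | ~0 | ~0 |
| 10% | 200 | 20 | ~0 | 2.1% | ~100% |
| 10% | 500 | 50 | ~0 | ~0 | 59.3% |

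Within each uptake level the sites use the service equally readily, so any difference in label is due to size. It is large at a cut-off of 52, smaller at 12, and at most exp(−4) = 1.8% under any use in a year. If uptake were as low as 1% at a 200-presentation site, m = 2 and the any-use figure would be exp(−2) = 13.5%.

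**4. Precision of a share at a small site**

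For 10 contacts in 200 presentations, p = 0.05. The Wilson 95% limits are [p + z²/2n ± z√(p(1 − p)/n + z²/4n²)]/(1 + z²/n). With z = 1.96 this is (0.0596 ± 0.0317)/1.0192, or 2.7% to 9.0%. A share removes the dependence on size but is imprecise at the smallest sites.

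**The case against.** The strongest reply has three parts.

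**The cell is loose wording and does not specify an odds.** It never says ratio or odds, it contains an evident slip, and the Reach row uses the same 'compared to' phrasing to introduce a true denominator. Active plus inactive sites equals enabled sites, and the row above counts implemented sites separately, so active/enabled can be recovered. This stands: a reader might infer that an odds will be reported, but the article does not establish that. The mismatch between definition and measure remains, as does the silence on whether the other 16 facilities are intended settings.

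**Misclassification of small sites is not shown.** A reader might infer that small facilities will be called non-adopters. That needs an absolute cut-off well above zero, and none is given. An article may leave the cut-off to a fuller document, so its absence alone is no fault. This also stands, and the point is therefore a risk of confounding. However, the article does fix the criterion itself, volume, in two places without tying it to facility size.

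**Size-adjusted use is already planned, and strategies rest on more than this row.** Contacts over presentations appear under Reach, and Phase 3 also draws on survey, interviews and a forum. This limits the damage. It does not correct the adoption comparison by facility type, and it shows that the better measure can be had from planned data.

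**Conclusion.** The concern holds in a limited form. The adoption row does not measure what it defines, and its activity criterion depends on facility size and time enabled, so the comparison of adoption by facility type can be confounded with size.

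The size of the effect cannot be fixed from the article. Under the assumed Poisson model, the difference in labelling between equally willing sites ranges from nearly total at a cut-off of 52 a year to at most 1.8 percentage points under any use in a year, for uptake of 2% to 10%. The choice of 87 or 103 as denominator moves an assumed 70 active sites by 12.5 points.

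Two stronger inferences are not supported. One is that the measure overstates adoption: 4.12 and 80.5% are on different scales, so neither inflates the other. The other is that the results could not be compared with other evaluations using the same framework, since nothing in the article allows that to be judged.

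The measure is descriptive, but it answers a named research question and the correction is cheap, so the change should be made.

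**What to change.** 1. In Table 2, replace the single comparison with two proportions: enabled sites out of 103 (availability) and active sites out of enabled sites (adoption). Report both overall and by facility type and region, for each service.
2. Define activity by CC contacts as a share of the facility's presentations over a fixed period since enablement. Set the cut-off before data extraction.
3. Add a sensitivity analysis at a second cut-off, or with any use in the period.
4. Amend the sentence under Phase 1: command centre service data analyses so that episode volume alone no longer stands for adoption.

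A rule that counts months with at least one contact should not be taken as free of size. Requiring 9 of 12 months, at 5% uptake and 200 presentations a year, gives a monthly mean of 10/12 = 0.83 and a monthly chance of 1 − exp(−0.83) = 0.57. The binomial chance of at least 9 such months is about 16%, against practically 100% at 30,000 presentations.

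Cost: wording in two places and no new data item, since presentations are already planned for Reach. The cut-off remains a judgement, which the sensitivity analysis exposes. Shares at very small sites are imprecise, so numerators and denominators should be shown with them.
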